### Sample size

This trial will examine exenatide QW, a weekly GLP1-RA, added to dapagliflozin versus sham saline injection added to dapagliflozin for an intervention period, of 32 weeks compared with a control group (placebo tablet and sham injection).

**Arm A:** Placebo tablet once daily and sham injection once weekly.**Arm B:** SGLT2 (dapagliflozin 10 mg once daily plus sham injection once weekly).**Arm C:** SGLT2+GLP1 RA (dapagliflozin 10 mg plus exenatide 2 mg once weekly injection).

The sample sizes have been calculated in order to conduct the following two comparisons:

Arm B (dapagliflozin) vs A (placebo).Arm B (dapagliflozin) vs C (dapagliflozin and exenatide).

These comparisons are selected to answer the key question of interest; although the study will not provide comparisons between arms C and A, nor will they be reported.

The original sample size calculation was carried out using Stata V.14 software (Stata Statistical Software: Release 14. College Station, Texas, USA: StataCorp LP). For both comparisons, a 1.5 kg in the change in body fat mass is considered a clinically relevant difference. From previous data, the within patient SD for the change in total body fat between baseline and 32 weeks is estimated as 1.8 kg.^17^ From this, a between-patient SD of 2.55 kg was computed. Using a two-group test with equal means (assuming 80% power and one-sided 5% significance level), 36 patients per treatment arm were estimated to be required in order to adequately power the planned analysis (assuming effect size of 0.59). Using these calculations and an anticipated 10% attrition and patient dropout rate, the original sample size was set at 120 participants.

As a result of the COVID-19 pandemic, however, 15 active patients were lost to follow-up and a revised sample size calculation was implemented, reducing the original sample size from 120 patients to 110 randomised patients in order to maintain meaningful results within the remaining timeframe of the study. Using the same clinically relevant difference of 1.5 kg, significance level and power, the between-patient SD would be 2.42 kg, giving an effect size of 0.62. Assuming 80% power, a minimum of 33 patients per treatment arm are required. Allowing for an anticipated 11% attrition rate/dropout rate, a total of 110 patients are required (calculated using NQuery V.8.1.2.0).

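### The revised sample size keeps 80% power at 33 per arm only through an unsupported drop in the SD from 2.55 to 2.42 kg, and its dropout allowance does not fit 110 or the 15 losses already reported

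*Protocol article*

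**What the plan says.** All of this stands in the Sample size section of the protocol article.

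- **Target difference.** For both planned comparisons, "a 1.5 kg in the change in body fat mass is considered a clinically relevant difference".
- **Original SD.** From a cited source, "the within patient SD for the change in total body fat between baseline and 32 weeks is estimated as 1.8 kg". The section continues: "From this, a between-patient SD of 2.55 kg was computed".
- **Original size.** With the test specified as "assuming 80% power and one-sided 5% significance level", "36 patients per treatment arm were estimated to be required". A 10% dropout allowance brings the total to 120.
- **Reason for the revision.** Because of the pandemic, "15 active patients were lost to follow-up and a revised sample size calculation was implemented". The total is cut to 110 randomised patients so that the trial can finish in the time left.
- **Revised inputs.** Difference, significance level and power are unchanged, and "the between-patient SD would be 2.42 kg, giving an effect size of 0.62". The minimum is now 33 per arm.
- **Revised total.** "Allowing for an anticipated 11% attrition rate/dropout rate, a total of 110 patients are required".

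The section gives no source, interim variance estimate or covariate adjustment for 2.42 kg. It does not say whether the 15 lost patients count towards the 110.

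**The concern.** When the difference, the significance level and the power are all held fixed, only a smaller SD can reduce the number needed per arm. The SD does fall, by 0.13 kg, and no evidence is offered for the change. The only stated motive is the remaining study time, which bears on how many patients can be recruited and not on how variable fat-mass change is. The claim that the smaller trial still has 80% power therefore rests on an unsupported input.

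The dropout step raises a second question. The 11% allowance does not lead to 110 by the method that gave 120 in the original calculation. The same paragraph also reports more losses than 110 can absorb if 99 completers are needed. The power statement for the primary comparisons, and the article's claim under Strengths and limitations that the sample is large enough for the primary question, both depend on these figures.

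**Working it through.** **Inputs (all from Sample size).** Difference d = 1.5 kg; within-patient SD 1.8 kg; between-patient SD 2.55 kg (original) and 2.42 kg (revised); one-sided alpha 0.05; power 80%; 36 then 33 per arm; dropout 10% then 11%; total 120 then 110; 15 lost. Allocation is equal across three arms (Overall design).

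**1. Reproducing the plan's figures.**
- SD: 1.8 × √2 = 2.546, given as 2.55. Effect sizes: 1.5/2.55 = 0.588 (0.59) and 1.5/2.42 = 0.620 (0.62).
- Normal approximation: n = 2(1.645 + 0.842)² SD²/d² = 2 × 6.183 × SD²/2.25.
  - SD 2.55: 35.7, so 36 per arm (37 by the t test).
  - SD 2.42: 32.2, so 33 per arm (33 by the t test).
- Original total: 3 × 36 = 108; 108/0.90 = 120.

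Both per-arm figures reproduce at one-sided 5%.

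**2. Where 2.42 comes from.** Solving the one-sided 5% two-sample t test for the SD that gives 80% power at d = 1.5 kg:

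| n per arm | SD giving 80% power |
|---|---|
| 32 | 2.387 |
| 33 | 2.424 |
| 34 | 2.462 |

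The stated 2.42 equals the n = 33 solution to two decimals. By the normal approximation the n = 33 solution is 2.450, so the match is to the t test.

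**3. Power if 2.55 is kept.** Power = P(T > t₀.₉₅), where T is noncentral t with 2n − 2 degrees of freedom and noncentrality d/(SD√(2/n)).
- n = 33: noncentrality 1.5/(2.55 × √(2/33)) = 2.389; critical value 1.669; power 76.4% (normal approximation 77.2%).
- n = 36, the original design: 79.6% (normal approximation 80.3%).
- Difference detectable with 80% power at n = 33: 1.5 × 2.55/2.424 = 1.58 kg. At n = 36 it is 1.51 kg.

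Like for like, the cost is about 3 percentage points.

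**4. The dropout allowance.** Required completers: 3 × 33 = 99.
- Division, as in the original calculation: 99/0.89 = 111.2, so 112.
- 110 × 0.89 = 97.9, about one short of 99.
- 110 × 0.90 = 99, so 110 fits a 10% allowance.
- 99 × 1.11 = 109.9, so 110 follows if one multiplies up instead of dividing.

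**5. The 15 losses.** 110 − 99 leaves room for 11. Fifteen is 15/110 = 13.6%. Assuming the 15 are among the 110 and have no week-32 DEXA, at most 110 − 15 = 95 are evaluable, or 31.7 per arm:

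| SD | One-sided power | Difference detectable at 80% |
|---|---|---|
| 2.42 kg | 78.6% | 1.53 kg |
| 2.55 kg | 74.9% | 1.61 kg |

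Any further dropout lowers these powers.

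**The case against.** **The benchmark is itself uncertain.** Only 1.8 kg is sourced; 2.55 kg is computed from it. The text describes the 1.8 kg as the SD for the change in total body fat. If that already is the SD of change scores, the √2 step overstates the variance and 33 per arm would have about 96% one-sided power. This stands as a caution: 2.55 is the plan's own figure, not an independently secure one. It does not rescue 2.42, which neither reading produces.

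**Back-calculation is not stated.** A reader might infer from the match and the conditional wording that 2.42 was solved for. The text does not say so, and the point does not need it. The defect is a missing justification.

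**The effect is small.** This stands. The SD change alone costs about 3 points. The primary analysis also adjusts for baseline fat mass, which may recover a little precision.

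**The 11% mismatch is trivial.** Largely so. It amounts to one or two patients and follows from a common shortcut.

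**The 15 may lie outside the 110.** The text does not settle this. It would mean 125 randomised, more than the original 120, which sits badly with a reduction. The 15 are also described as active patients, and no replacement is mentioned. Inclusion is the likelier reading but remains an assumption.

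**A much larger shortfall might be inferred.** Adding a further 11% loss among the remaining 95 leaves about 28 per arm and 70% power at SD 2.55. No part of the article projects that second loss. Two-sided power would also be lower, but the calculation is explicitly one-sided and sidedness is a separate question.

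**Conclusion.** The point holds and should be fixed. The revised 80% power rests on an SD of 2.42 kg that the article does not support. With the plan's own earlier SD of 2.55 kg, 33 per arm gives about 76% one-sided power, against about 80% for the original design, and a detectable difference of about 1.58 kg.

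If the 15 lost patients are among the 110 and have no week-32 DEXA, the stated minimum of 33 per arm cannot be met. At most 95 would be evaluable, with power of about 75% to 79% depending on the SD, so the total shortfall is about 1 to 5 points before further dropout. Without that assumption, it cannot be said that the allowance is already exceeded. The 11% versus 10% discrepancy is minor.

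A reader might conclude that the trial is seriously underpowered, or that the oversight committees were misinformed. The documents support neither: the loss is modest, and nothing shows what the committees were given about the revision.

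**What to change.** Rewrite the revision paragraph in Sample size to do four things.

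1. Justify the SD. Either keep 2.55 kg, or use the blinded pooled SD of the baseline-to-week-32 DEXA fat-mass change in participants who have completed. If 2.42 kg is only the value at which 33 per arm would suffice, say so and do not offer it as an estimate.
2. State whether the 15 lost patients count towards the 110 and whether any has a week-32 DEXA.
3. Make the dropout figure agree with 110: 10% matches, whereas 11% implies 112.
4. Restate power and the detectable difference at the evaluable number that can be reached, at most 95 if the 15 are included.

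No extra enrolment, change in conduct or change to the primary analysis is needed. The cost is one paragraph and, optionally, one blinded variance calculation. The downside is a slightly lower stated power, unless the blinded SD turns out smaller than planned.

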### Screening, enrolment and randomisation

After giving written informed consent, potentially eligible participants will attend a screening visit within 6 weeks prior to randomisation; this includes a medical history to confirm the participant’s eligibility to participate as determined by the inclusion/exclusion criteria (table 1), physical examination, blood tests, urinalysis and an ECG. Each participant will be informed of his/her eligibility for the trial once all results are available (usually within 1 week from obtaining consent).

The randomisation for each stratum will be performed using computer generated (Treatment Allocation Randomisation System, TARDIS) random balanced blocks to ensure approximately equal numbers of participants across the treatment arms within each stratum. Each patient will be assigned a unique study identification number. The study is set-up as a double blind trial with both the participants, doctor, site and LCTC (Liverpool Clinical Trials Centre) RESILIENT trial teams being blind to the treatment received. Unblinded members of the research staff (pharmacy and selected research nurses) will remain the same throughout the trial. A blinded confirmation email will be sent to all relevant site staff and LCTC trial team detailing the trial number and patient initials. An unblinded confirmation email will also be sent to all relevant pharmacy staff detailing the allocated treatment arm, trial number and patient initials. Only the subject number and initials will be recorded in the electronic case report form (eCRF). All other patient identifiable data will be completely anonymised. An additional validation check has been built into the eCRF (MACRO 4) for authorised trial team members only to confirm eligibility and suitability to proceed to randomisation.

### Dosage and administration of study treatments

Participants will attend once a week for administration of a subcutaneous injection (exenatide QW 2 mg or sham injection) for the duration of the study (32 weeks). The exenatide QW injection and the sham injection are not identical in appearance, so to maintain the study blinding, medication dispensed will be given to a member of the unblinded research team in an opaque bag to ensure the contents cannot be seen by members of the blinded research team or the patient. No blinded staff member will be allowed in the room at the time of injection and the injection will be disposed of by unblinded staff members in line with local protocols, and in a concealed manner. Participants will also be instructed to take a tablet with water (dapagliflozin 10 mg or matching placebo) each morning for the duration of the study, while continuing with their usual medication and attending for scheduled study visits. The number and size of tablets will be identical for the investigational products (dapagliflozin 10 mg and placebo). Participants will be asked to return all unused investigational products, including any empty medication packages to the clinic at each visit. The subject’s compliance will be discussed at each study visit and assessed based on the number of injections administered and returned counts. This will be recorded in the defined CRF. To aid compliance, participants will be asked to complete a patient diary. Participants judged to be non-compliant may continue in the study, but will be counselled on the importance of taking their study medication as prescribed.

### Study visits and procedures

#### Anthropometric measurements

Body weight and height, waist and hip circumference and whole-body bioimpedance analysis (TANITA: total body mass, fat percentage, fat mass, fat free mass and muscle mass) will be recorded. Blood pressure will be measured from the left arm after patients have been seated for 5 min. The first reading will be discarded, and the mean of three subsequent readings recorded (table 2).

**Table 2 T2:** Assessments and procedures during screening and study visits (D, day; W, week)* Not including administration of weekly exenatide QW/sham injection

Procedure	D −42–2 (including washout if necessary)	D −14–0	D 0	W 2	W 4	W 8	W 12	W 16	W 20	W 24	W 28	W 30–32
Visit (fasting)	0		1 and 2	3	4	5	6	7	8	9	10	11 and 12
Informed consent	X											
Medical history/demographics	X											
Physical examination and ECG	X											
Pregnancy test	X		X									
Glucometer dispensing and training	X											
Urinalysis	X											
Height	X											
Weight	X		X	X	X	X	X	X	X	X	X	X
Waist and hip measurements			X	X	X	X	X	X	X	X	X	X
Bioelectrical impedance analysis (BIA)			X	X	X	X	X	X	X	X	X	X
BP, pulse	X		X	X	X	X	X	X	X	X	X	X
Blood tests	X		X	X	X	X	X	X	X	X	X	X
Dapaglifozin/placebo dispensing			X		X	X	X	X	X	X	X	X
Concomitant medication check	X		X	X	X	X	X	X	X	X	X	X
Compliance check				X	X	X	X	X	X	X	X	X
AE reporting			X	X	X	X	X	X	X	X	X	X
24-hour urine			X		X			X				X
4-day food diary			X		X			X				X
4-day activity monitoring			X		X			X				X
Test meal			X		X			X				X
Indirect calorimetry			X		X			X				X
Psychological questionnaires and VAS			X		X			X				X
DEXA			X									X
MRI (full body, liver fat, pancreatic fat)			X									X
MRI cardiac			X									X
fMRI and eye-tracking		X										X
FMD			X									X
Cardiac ECHO			X									X
DLW and additional DEXA		X	X		X			X				X
Euglycaemic clamps			X									X

*Not including administration of weekly exenatide QW/sham injection.

AE, adverse event; BIA, bioelectrical impedance analysis; BP, blood pressure; DEXA, dual-energy X-ray absorptiometry; DLW, doubly labelled water; ECG, electrocardiogram; FMD, flow-mediated dilatation; fMRI, functional MRI; VAS, Visual Analogue Scale.

#### Biochemical measurements

All patients will have a routine blood sample taken for HbA_1c_, fasting plasma glucose, renal profile (to include electrolytes, urea and creatinine, and eGFR), lipid profile, liver function tests (to include ALT, AST and bilirubin) and insulin. Insulin sensitivity will be measured by Homeostatic Model Assessment for Insulin Resistance (HOMA-IR).^18^ eGFR will be estimated using the Modification of Diet in Renal Disease (MDRD). We will measure fasting plasma glucose (FPG) and estimated glomerular filtration rate (eGFR) every 2–4 weeks. This will allow us to determine the amount of filtered glucose calculated from the product of the FPG (mg/dL) and eGFR (mL/min/1.73 m^2^).

#### Test meal visits (visits 1, 4, 7 and 11)

Test meal visits will take place at baseline and after 4, 16 and 32 weeks of treatment (tables 2 and 3). Participants will be asked to attend the investigational unit at 08:00, having had nothing to eat or drink other than water from midnight. Participants’ anthropological and biochemical measurements will be taken (see above). An explanation and demonstration of Visual Analogue Scale (VAS) questionnaires, appetite questionnaires and ventilated hood will be given. Additional measures taken during test meal days are described below.

**Table 3 T3:** Test meal guidelines

Time point guidelines	Procedure
Arrival 08:00*	Blood sample taken. Subjects asked to empty bladder; start of timed 24-hour urine collection. Weight, waist circumference, bioelectrical impedance analysis, pulse and blood pressure taken.
08:10	Basal metabolic rate measurement (indirect calorimetry—see below for details).
08:55 (T1 VAS)	Subjects will complete a pre-breakfast, seven-component VAS questionnaire to measure hunger and other subjective variables.
09:00	Subjects will be provided with a fixed-quantity breakfast, consisting of cornflakes with milk, toast and preserve, tea/coffee and orange juice.
09:20 (T2 VAS)	Subjects will complete a post-breakfast, 7-component VAS questionnaire to measure hunger and other subjective variables.
10:00, 11:00, 12:00 (T3-5 VAS) *Administered at hourly intervals (from pre-breakfast VAS) for 3* hours	Subjects will complete the same seven-component VAS questionnaire as used pre-breakfast, providing a pre-meal set of ratings.
12:55 (T6 VAS)	Subjects will complete a pre-lunch, seven-component VAS questionnaire to measure hunger and other subjective variables.
13:00	Subjects will be given an ad libitum lunch. The meal consists of a multiple item buffet (mix of high-fat and low-fat savoury items) and subjects may eat ad lib, and signal when they have finished the meal.
13:30 (T7 VAS)	Subjects will complete a post-lunch, seven-component VAS questionnaire to measure hunger and other subjective variables. Participants also complete a post-lunch palatability VAS.
14:00, 15:00, 16:00, 17:00 (T8-11 VAS) *Administered at hourly intervals (from pre-breakfast VAS) for 4* hours	Subjects will complete the same seven-component VAS questionnaire as used pre-breakfast, providing a post-meal set of ratings.

*Timings will be adjusted to facilitate an amended arrival time. All events will remain at the same relative intervals.

VAS, Visual Analogue Scale.

#### Food intake and eating behaviour

Participants will be provided with a fixed load breakfast (providing 25% energy from estimated Resting metabolic rate (RMR)) followed 4 hours later by an *ad libitum* lunch, which they will self-serve. The *ad libitum* lunch will consist of a multiple item buffet (eg, high and low calorie, sweet and savoury items) to understand how the potential satiety and reward-based changes in appetite effect energy intake and modify food choice. Pen and paper VAS measures of appetite (hunger, fullness, desire to eat, prospective consumption, satisfaction, thirst and nausea) fluctuations throughout the day will also be collected with retrospective appetite and craving questionnaires at the end of the day. Taken together, these data fully characterise drug effects on appetite and eating behaviour.

A range of questionnaires assessing secondary outcomes of appetite, cravings, feelings of control and eating behaviours (including food choice) will also be completed at test meal visits. These include the Three Factor Eating Questionnaire (TFEQ)^19^; Power of Food Scale (PoF)^20^; the Craving for Sweet Foods sub-questionnaire from the Health and Tastes Attitude Scale (HTAS)^21^; the 7-day Control of Eating Questionnaire (COEQ)^22^; the external eating subscale from the Dutch Eating Behaviour Questionnaire (DEBQ)^23^ assessing external eating; and the Mindful Eating Scale (MES)^24^ describing the physical and emotional sensations associated with eating.

#### Indirect calorimetry

Energy expenditure and respiratory quotients will be measured on the morning of the test meal visit prior to the fixed energy breakfast using an indirect calorimeter (GEM Nutrition, Daresbury, UK) fitted with a ventilated hood and derived using the modified Weir equation.^16^ Participants will remain awake but motionless in a supine position for 45 min with RMR calculated from respiratory data averaged over the final 30 min of assessment. The first 15 min of each measurement will be discarded to allow for complete acclimatisation to the hood and the recumbent position.

#### Physical activity monitoring

Habitual physical activity will be monitored using a SenseWear mini armband (BodyMedia, Pittsburgh, Pennsylvania, USA) for a 4-day period (to include one weekend day) during weeks 0, 4, 16 and 32. Data collected from the SenseWear device include daily average step count, total energy expenditure, active energy expenditure and time spent in domains of physical activity including sleep, lying, sedentary (<1.5 metabolic equivalents, METS), light (1.5–3 METS), moderate (3–6 METS), vigorous (6–9 METS) and very vigorous (>9 METS) and is analysed using SenseWear Professional software (V.8.0).

#### Food diaries

Participants will be asked to complete a food diary detailing exactly what they eat and drink over the same 4 day period. Total energy consumption, carbohydrate, protein and fat content will be determined from dietary records using Nutritics (Nutrition Analysis Software for Professionals).

### Baseline and end of treatment measures

#### Body composition

All participants will undertake a full body DEXA (Lunar IDXA, GE Healthcare, Amersham, UK) scan after an overnight fast at baseline and week 32. Body composition will be determined to quantify total and regional (trunk, limb, android and gynoid) fat mass and fat-free mass.

MRI measures of body composition, hepatic and pancreatic fat MRI eligible participants will be scanned using a 3.0 T Siemens Prisma scanner (Siemens Medical Solutions, Erlangen, Germany) at the Liverpool MRI Centre (LiMRIC). Images are obtained with the patient supine and using an integrated body coil (Siemens Medical Solutions, Erlangen, Germany).

For body composition, multiple blocks of contiguous slices using a Dixon VIBE in and out of phase sequence will be conducted to produce fat and water images from the vertex of the skull to the knees. These will be used to determine fat volumes in abdomen and neck. For hepatic fat, a multi-echo Dixon sequence with blocks of contiguous slices and breath holds on expiration will be used to image the abdomen. A single transverse slice that intersects the porta-hepatis will be positioned and a multi-echo gradient-echo image will be acquired to determine a liver fat fraction. For the assessment of pancreatic fat, circular regions of interest (~100 mm^2^) will be drawn in the head, body and tail of the pancreas of two representative slices, with fat fraction calculated as the average across both slices.

